#### Independent variables

Presence of prothrombotic defects: Following specific prothrombotic defects were studied: deficiency of AT, PC, PS; elevated levels of coagulation factors II, VIII, IX and XI; FVL; PT and MTHFR gene mutation; elevated levels of Lp (a), Hcy and APLAPresenting laboratory features (Complete blood count, total white cell count, peripheral blast count, hemoglobin, platelet count)Age of the patient at the time of diagnosis of ALL (age ≥ 10 years, age < 10 years)Risk categorization of ALL (HR/VHR, SR)Therapy Variables: Type of ASP (*E. coli*, PEG ASP)Phase of therapy: Consolidation II versus other phases

### Data collection

#### Clinical data

Specific case report forms (CRF) were created for data collection for all patients. In summary, data included baseline patient characteristics, personal and family history of thrombosis or prothrombotic disorder; any known risk factors (smoking, dyslipidemia, thrombophilia), details of CVL, diagnosis of ALL and ALL-therapy.

#### Laboratory data

Blood samples were tested for complete blood count (CBC), coagulation parameters (INR, PTT, fibrinogen and D-dimer) and prothrombotic defects. For the purpose of this study the prothrombotic defects were divided as follows: **“Variable” defects:** defects in those hemostatic proteins the levels of which are influenced by the exogenous factors like inflammation or anti-leukemic therapy (e.g. ASP and steroids). Deficiency of AT, PC, PS; elevated levels of coagulation factors II, VIII, IX and XI; elevated levels of Lp (a), Hcy and APLA were considered as “variable” defects. **“Non-variable” defects:** those prothrombotic defects, the estimation of which is unlikely to be affected by exogenous factors. These defects include FVL, PT and MTHFR gene mutation. Details of wild type, heterozygous and homozygous state will be collected.

#### Diagnosis, evaluation and management of patients with symptomatic TE

Symptomatic TE was a prospectively defined adverse outcome on DFCI ALL 05–01 study. To ensure uniformity of diagnosis and evaluation, uniform guidelines for the definition of symptomatic TE and clinical and radiological assessment at the time of diagnosis of TE were used as outlined in Table 2. At the time of diagnosis of TE, laboratory evaluation included CBC, coagulation profile (INR, APTT, D-dimer fibrinogen) and measurement of “variable” prothrombotic defects. Patients who develop symptomatic TE were managed according to the recommended uniform guidelines developed for management of TE for DFCI ALL 05–01 study. Details of clinical, laboratory and imaging studies, management and, outcome of TE were recorded on the CRF.

### Assays for hemostatic factors

#### Timing of blood test

Blood samples for prothrombotic defects were collected for all patients prior to starting ALL therapy. For Hcy and Lp(a) estimation overnight fasting blood sample were used. Testing for prothrombotic defects were done on the day of the scheduled lumbar puncture avoiding additional fasting.

#### Sample collection

Detail blood sample collection and processing protocol was developed and provided to the study sites. In short, blood was collected into one 3.2% Sodium citrate tube (~ 1.8 mL) and one EDTA tube (~1.8 mL). Within 30 min of collection, blood was centrifuged to separate platelet poor plasma which was aliquoted and frozen at –70 °C until the time of assay. Citrated sample was used for measurement of factors II, VIII, IX and, XI; AT, PC, and PS; D-dimer, Lp(a) and APLA. EDTA sample was used for Hcy assay. Buffy coats will be used for DNA analysis.

#### Laboratory assays

To avoid inter-laboratory variation, all samples for prothrombotic defects were assayed at centralized location namely the Hemostasis Reference Laboratory (HRL) at Henderson Research Center, Hamilton using standardized procedures http://www.hemostasislab.com. Blood samples collected from patients at other centers were couriered on dry ice to HRL. In addition, CBC, differential, peripheral blast count, and coagulation parameters (PT, APTT, fibrinogen) were performed at individual institution. Samples for prothrombotic defects were assayed in batches.

### Clinical and laboratory follow-up, study duration and study withdrawal criteria

#### Clinical follow up

After initial hospitalization for evaluation and induction therapy for ALL, all patients were seen at least weekly (or more frequently if needed) at the outpatient clinics as a part of routine clinical care. This study required no visits above and beyond those required for this clinical care. Details of hospitalization and other complications including TE during the study-period and modification of ALL-therapy, if any, were recorded. Patients were monitored for failure of remission induction, recurrence of ALL, stem cell transplantation and continued enrollment on DFCI 05–01 study. The clinical follow-up and data collection for the proposed study was linked to DFCI ALL 05–01 study monitoring and follow up.

#### Study duration

Patients were followed for development of symptomatic TE till the completion of ALL-therapy on DFCI 05–01 study which is two years and one month.

#### Study withdrawal criteria

Patients were withdrawn from thrombophilia study if they failed to achieve remission, develop recurrence of ALL while on ALL-therapy, if they needed stem cell transplantation or were withdrawn from DFCI 05–01 study for any reason.

### Time frame of the study

The anticipated total study period was four years. During first two years of the study, patient enrollment including initial data collection and blood sampling were planned to be completed. Patient follow-up continued at respective center till the completion of ALL-therapy (~ 2 years) as scheduled on DFCI 05–01 study.

### Outcomes

#### Primary outcome

Diagnosis of symptomatic TE in any location while on active ALL-therapy.

#### Secondary outcomes

Includes detection of at least one prothrombotic defect, completion of ALL-therapy or withdrawal from DFCI 05–01 study and recurrence of disease or death due to any cause while on DFCI 05–01 ALL-therapy.

#### Justification for inclusion of symptomatic TE

Clinical significance of asymptomatic TE detected by screening methods is so far unknown. Further, by inclusion of only symptomatic and objectively confirmed TE, we will avoid ambiguity over diagnosis, and thus, reporting of TE. Also the inclusion of only symptomatic TE will avoid invasive (e.g. venography) and non-invasive (e.g. ultra-sonography) tests to screen for asymptomatic TE. This, we hope, will improve patient and physician compliance and participation in the study.

#### Criteria for diagnosing symptomatic TE

Objective testing must be done to confirm suspected thrombotic events in symptomatic patient (Details in Table 2). Acceptable objective tests for diagnosis of CNS TE: cerebral angiographies, contrast enhanced magnetic resonance imaging (MRI), MR arteriography (MRA) or MR venography (MRV); deep venous thrombosis (DVT) include: venography, Doppler ultrasonography (USG), contrast enhanced computerized tomography (CT), MRV; for PE: pulmonary angiography, ventilation/perfusion (V/Q) scan or spiral CT scan; and for right atrial TE: echocardiography (ECHO). DVT was diagnosed by detection of echogenic material within the lumen of a vein on a gray scale and presence of partial or complete absence of flow by pulse wave or color Doppler ultrasonography or if venography or contrast enhanced CT shows a persistent intraluminal filling defect [9, 56, 57]. CNS-TE was diagnosed if imaging modalities showed intraluminal arterial or venous filling defect/s with or without associated cortical changes. PE was confirmed with intraluminal filling defect or abrupt cut-off or non-filling of an arterial segment on either pulmonary angiograpghy or spiral CT scan or a high probability V/Q scan.

#### Criteria for diagnosing prothrombotic defect

Age-adjusted standardized laboratory data were used for classification of protein deficiencies (PC, PS, AT) or elevation (F II, VIII, IX, XI) and risk cutoffs [Lp (a), Hcy, APLA]. For this purposes the age-adjusted laboratory normal values based on Canadian population data were used [58]. The actual value was categorized as deficiency, normal range or elevation of the factor studied. Identification of the gene mutation will confirm FVL, PT and MTHFR polymorphism.

### Statistical considerations

#### Study variables

Continous variables will be age, levels of factors II, VIII, IX and XI; PC, PS, AT; Lp (a), and Hcy. Categorical variables will be gender (male/female); ALL risk categories (VHR/HR/SR); ASP type (*E. coli*/PEG); details of CVL (presence/absence),“non-variable” prothrombotic defects (FVL, PT and MTHFR mutation) (presence/absence).

#### Methods for analysis

Patient demographics, prognostic characteristics and clinical outcome will be summarized using descriptive measures expressed as mean (standard deviation) or median (minimum, maximum) for continuous variables and number (percent) for categorical variables. The analysis will adopt the intention-to-treat principle. Since TE is a safety outcome for ALL-therapy we will also perform “per-protocol” analysis. Association between categorical outcomes and groups will be assessed using Fisher’s Exact test or chi-squared test. Thrombosis-free survival will be estimated using Kaplan-Meier method. The limit for statistical significance will be set at α = 0.05. In all comparison, 95% confidence intervals (CI) of the measure of association between groups will be reported.

Logistic regression will be used to analyze data for both primary and secondary outcomes. Analysis results of regression modeling will expressed as coefficient, corresponding standard error, 95% CI and associated *p*-values. Variance inflation factors will be used to assess multi-colinearity among predictors. Model assumptions will be assessed through residual analysis. Goodness-of-fit will be evaluated using qq plots for normality and coefficient of determination and R^2^ for regression models. Some of the time dependent confounding variables like infection or CVL-related problems (which may influence the risk of TE) are unpredictable and hence cannot be adjusted prospectively. To compensate for that we will prospectively collect the information and enter in the regression model when risk factors for thrombosis are being analyzed. All analyses will be performed using SPSS 14 software (2005 SPSS Inc). Table 3 provides a summary of specific methods of analysis for primary and secondary outcomes.

**Table 3 Tab3:** Proposed Methods of Analysis

Analysis	Hypothesis	Independent variable	Outcome variable		Method of analysis
			Name	Variable type	
Primary	Presence of one or more prothrombotic defect/s increase the risk of TE	Presence of one or more prothrombotic defect	Symptomatic TE	Binary	Fisher’s Exact Test Analysis performed for overall prevalence of at least one prothrombotic defect and for individual defect.
Secondary					
Aim 1.	1.a Older age increases the risk of TE, especially in presence of one or more prothrombotic defect	Age of the patient (age < 10 years, age ≥ 10 years)	Symptomatic TE	Binary	Logistic regression
	1.b HR/VHR ALL increases the risk of TE, especially in presence of one or more prothrombotic defect	Risk categorization of ALL (HR/VHR ALL, SR ALL)			
	1.c PEG ASP therapy increases the risk of TE, especially in presence of one or more prothrombotic defect	Type of ASP (*E. coli* ASP, PEG ASP)			
Aim 2	A mathematical model can be used to determine the risk of symptomatic TE	Clinical Variables: age of the patient, risk categorization of ALL presence or absence of prothrombotic defect, Therapy variable: type of ASP used	Symptomatic TE	Binary	Regression analysis will be used to predict the risk of TE
Aim 3	The overall (presence of at least one tested) prevalence of one or more prothrombotic defect is at least 20%		Prevalence of one or more prothrombotic defect/s	Categorical	Prevalence of individual and overall prothrombotic defect will be expressed as percentage of affected patients with 95% CI

Logistic regression will be used to analyze the data for both primary and secondary outcomes. Analysis results of regression modeling will be expressed as coefficient, corresponding standard error, 95% CI and associated *p*-values. Variance inflation factors will be used to assess multi-collinearity among predictors. Missing values will be handled using multiple imputation or last observation carried forward. Model assumptions will be assessed through residual analysis. Goodness-of-fit will be evaluated using qq plots for normality and coefficient of determination and R2 for regression models

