## Background

Acute lymphoblastic leukemia (ALL), the most common cancer in children, is now curable in over 80% of the children with current aggressive therapy [1, 2]. However, such therapy is associated with significant, sometimes fatal, complications. These therapy-related morbidity and mortality can limit the dose intensification of antileukemic agents and compromise the prospects of cure [3]. Thus, to improve the cure-rates and quality of life of children with ALL, it is important to reduce specific, avoidable therapy-related complications.

Thromboembolism (TE) is one such serious complication in association with ALL therapy in children [4, 5]. Overall TE is rare in general pediatric population with ~0.19 events per 10,000 children [6–8]. In contrast, children with ALL are at much higher risk for TE; reported incidence of symptomatic TE varies from 1% to 14% and that for asymptomatic TE is up to 37% [4, 5, 9]. The majority of the symptomatic TE occur in potentially fatal sites, ***~***50% in the central nervous system (CNS), 2% pulmonary embolism (PE) and 2% in the right atrium [4, 5]. TE including CNS-TE is associated with significant morbidity. In addition, development of TE interferes with the scheduled ALL-therapy; such interruptions are known to compromise cure rates [5, 10]. The average case fatality ratio from TE in children with ALL is 15% [5]. With ~15–20% all-cause mortality in children with ALL; TE may be an important cause of death during ALL-therapy [5, 11].

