Our preliminary studies indicate that children who develop TE are more likely to have adverse outcome from ALL compared to those who do not develop TE. Silverman et al., on DFCI 91–01 study showed that early (< 25 weeks) discontinuation of ASP-therapy adversely affected 5-year event free survival (EFS) (73% vs. 90%; *p* < 0.01); CNS event or non-CNS-TE was responsible for early discontinuation of ASP in 20% of patients [10]. We observed 27% (3/11) mortality in children with ALL and TE compared to 6% (5/84) in children with ALL without TE (*p* = 0.048; 95% CI -5.5, 48.1).

There is no information about thrombophilia in patients treated on DFCI studies. At McMaster University, 10 of 12 patients with ALL and symptomatic TE were evaluated for prothrombotic defects; 9 had abnormal thrombophilia profile and 6 patients had >1 defect. Nine patients had increased levels of factor VIII:C (mean 3.2 U/mL; range 2.11–5.8); 3 patients had elevated fasting Lp (a) levels, one each had increased fasting Hcy level, reduced PS levels, AT deficiency and one was heterozygous for MTHFR C677T. Although the sample size is small and the prothrombotic work-up was performed after the detection of TE, this data strongly support detail evaluation of inherited and acquired prothrombotic defects as a potential risk factor for ALL-associated TE.

In summary, TE is a significant complication in children with ALL. Prothrombotic defects are shown to be prevalent in ~20% of children with ALL. Leukemia and its therapy can potentially exacerbate the deleterious effects of prothrombotic defects even in heterozygous individuals. However, the extent of the risk, if any, predisposed by prothrombotic defects in the development of TE in children with ALL (especially in relation with ALL-therapy) is unknown. Hence we propose a thrombophilia study within the context of DFCI ALL 05–01 randomized controlled trial (RCT). The proposed thrombophilia study will evaluate the role of prothrombotic defects in the development of TE as well as the interaction, if any, of these defects with patient (e.g. age), disease (e.g. risk-categorization) and therapy (e.g. the type of ASP) variables.

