#### Sample size

The sample size calculation is based around the primary aim of the study. The null hypothesis for the primary aim of this study that there is no difference in the proportion of patients developing TE with or without prothrombotic defect. The criterion for significance is set at two sided α = 0.05. *Minimal clinically important difference (MCID):* The purpose of this study is to identify a population at high risk for TE, so that we can develop strategies for prevention of TE. The MCID we wish to detect will be guided by the numbers needed to treat (NNT) to prevent one event of TE. If we have to use presence of prothrombotic defect as the only criteria for effective thromboprophylaxis, we aim to detect a MCID of at least 25%. This will mean that, we will need to treat ~4 patients to prevent one event of TE. Table 4 outlines the required sample size calculation and NNT at various levels of MCID. Based on the preliminary data from Canadian institutions on previous DFCI protocol 20–01, the incidence of TE is estimated to be 11%. Based on previous studies, the overall prevalence of prothrombotic defect (presence of at least one prothrombotic defect) in the study cohort is estimated to be 20% [38, 39, 48]. With a sample of 150 patients (30 patients with and 120 without prothrombotic defect) there is more than 80% chance of detecting MCID of 25% at a two-sided significance level of 0.05.

**Table 4 Tab4:** Sample size calculation requirements to compare cumulative TE in patients with and without prothrombotic defects

δ	Sample size for each group	Estimated sample size for proposed study (α =0.05 and β = 0.2, with 20% prevalence of prothombotic defects based on previous studies [12])			Number of patients needed to treat to prevent one event of TE (NNT)
		With PD	Without PD	Total	
0.40	16	16	80	96	approximately 3 patients
0.30^a^	24	24	120	144	approximately 4 patients
0.20	41	41	205	246	5 patients
0.10	102	102	510	612	10 patients

^δ^Difference in the cumulative incidence of TE in patients with and without prothrombotic defects

^a^Minimal clinically important difference

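### A per-protocol analysis and last observation carried forward fit this cohort badly: the first can drop TE cases, the second has no sound use

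*Protocol article*

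**What the plan says.** All references are to the protocol article.

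- **Analysis sets (Methods for analysis).** "The analysis will adopt the intention-to-treat principle". The next sentence begins "Since TE is a safety outcome for ALL-therapy we will also perform" and names a per-protocol analysis. No per-protocol set is defined, and no comparison is named for it.
- **Missing data (Table 3 footnote).** "Missing values will be handled using multiple imputation or last observation carried forward". The variables are not named, nor when each method applies.
- **Methods by aim (Table 3).** Fisher's exact test for the primary comparison and logistic or other regression for secondary aims 1 and 2, all on TE as a binary outcome. Kaplan-Meier thrombosis-free survival is planned in the text above the table, but Table 3 gives no time-to-event method to any aim.
- **Withdrawal (Study withdrawal criteria).** "Patients were withdrawn from thrombophilia study if they failed to achieve remission, develop recurrence of ALL while on ALL-therapy"; transplantation and leaving DFCI 05–01 for any reason also count. TE is not a listed reason.
- **Effect of TE on therapy.** The Background says that "development of TE interferes with the scheduled ALL-therapy". The section on preliminary DFCI results reports from an earlier DFCI study that "CNS event or non-CNS-TE was responsible for early discontinuation of ASP in 20% of patients".
- **Timing.** Samples for the defects were taken in all patients before therapy (Timing of blood test). Follow-up for TE runs to the end of therapy, two years and one month (Study duration).

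**The concern.** Intention-to-treat and per-protocol describe how to handle departures from an assigned treatment. The primary contrast here is between children with and without a prothrombotic defect, which nobody assigns. Only asparaginase type is randomised, and that is a secondary factor. The reason given does not help: if TE is a safety outcome, that argues for counting it in every treated child, not for restricting the analysis to children who kept to the schedule.

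The restriction may also be harmful. By the article's own account TE changes therapy. A set made up of children treated as planned would then be selected partly on a consequence of the outcome, and some TE cases could leave the analysis because they had TE.

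LOCF needs a repeated measurement with an earlier value to carry. The defects are classified from pre-therapy samples, and the outcome is one event that happens or does not. The only thing to carry forward for a child withdrawn without an event is the absence of TE, which treats an unobserved period as event-free. The Fisher and logistic analyses do the same if withdrawn children stay in the denominator.

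At stake are the TE incidence and the risk difference, from which the Sample size section derives the NNT that is meant to guide prophylaxis.

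**Working it through.** **Inputs (Sample size, Feasibility).** 30 children with and 120 without a defect; TE incidence 11%; defect prevalence 20%; MCID 25 points; two-sided α 0.05; about 5% withdrawal from DFCI 05–01.

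**1. The plan's own figure.** Take 11% as the overall incidence. Without a defect, p₂ = 0.11 − 0.20 × 0.25 = 0.06; with a defect, p₁ = 0.06 + 0.25 = 0.31. Power for 30 vs 120 is 92.4% (normal approximation) or 92.2% (exact enumeration of the Fisher test). If 11% is read as the risk without a defect (36% vs 11%), power is 86.9% or 84.5%. Both readings agree with the stated power above 80%, so no figure in the plan is disputed.

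**2. A per-protocol set that loses TE cases.** Expected events are 30 × 0.31 = 9.3 and 120 × 0.06 = 7.2. Drop a share r of TE cases and nobody else. The risk in a group of size n becomes n·p(1 − r) / (n − n·p·r). At r = 0.5: 4.65/25.35 = 18.3% and 3.6/116.4 = 3.1%. The shares are assumptions; the documents give none.

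| Share of TE cases dropped | Events left | Risks | Difference (points) | Risk ratio | Fisher power |
|---|---|---|---|---|---|
| 0 | 16.5 | 31.0% vs 6.0% | 25.0 | 5.17 | 92% |
| 10% | 14.9 | 28.8% vs 5.4% | 23.4 | 5.30 | 89% |
| 20% | 13.2 | 26.4% vs 4.9% | 21.6 | 5.44 | 87% |
| 50% | 8.2 | 18.3% vs 3.1% | 15.3 | 5.93 | 69% |
| 80% | 3.3 | 8.2% vs 1.3% | 7.0 | 6.54 | 33% |

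**3. The odds ratio.** Let a and c be the TE cases, and b and d the non-cases, with and without a defect. If a fraction s₁ of cases and s₀ of non-cases is kept, whatever the defect status, the odds ratio is (a·s₁ × d·s₀)/(b·s₀ × c·s₁) = ad/bc, so it is unchanged. In whole patients, 9/30 vs 7/120 gives (9 × 113)/(21 × 7) = 6.92, risk ratio 5.14, difference 24.2 points. Keep 50% of cases and 90% of the others: 4.5/23.4 vs 3.5/105.2. The odds ratio is (4.5 × 101.7)/(18.9 × 3.5) = 6.92, the risk ratio about 5.8, the difference 15.9 points.

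**4. LOCF applied to TE status.** Let a share w withdraw, equally in both groups. The worst case is that all of their TE risk lies after withdrawal. Then p₁ becomes 0.31(1 − w) and p₂ becomes 0.06(1 − w). At w = 0.05: 0.2945 − 0.057 = 0.2375, so the difference falls from 25.0 to about 23.8 points, a loss of 1.25. The risk ratio stays at 5.17 and Fisher power is 91%. At w = 0.20 (assumption) the difference is 20.0 points and power 85%. If withdrawal were unequal, say 10% with and 5% without a defect (assumption), the difference would be 0.279 − 0.057 = 22.2 points and the risk ratio 4.90.

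In events: 5% of 150 is 7.5 children. At 11% they carry 7.5 × 0.11 ≈ 0.8 expected TE, and at the 17% quoted for high-risk disease 7.5 × 0.17 ≈ 1.3, against 16 anticipated in the Feasibility section.

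**The case against.** The strongest reply is that the plan does not say what a critic fears. The per-protocol set is undefined, it supplements the main analysis, and a condensed article may leave its definition to the full protocol. It may be meant for the randomised asparaginase comparison, where the term has a use. LOCF is one of two options in a footnote about regression and is not tied to TE. Some data are repeated: the variable defects are measured again at TE diagnosis, and infections and line problems are recorded over time. Kaplan-Meier estimation, which censors, is already planned.

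Most of this stands, and it rules out several stronger readings:

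- A reader might infer that TE cases will be removed, or that withdrawn children will be coded TE-free. No section says either.
- A reader might infer bias toward no association. That holds for the risk difference only; the odds ratio is unchanged when dropping depends on TE alone, and the risk ratio moves away from 1.
- A reader might take the 20% from the earlier DFCI study as the share of TE patients whose therapy changed. It describes reasons for stopping asparaginase early.
- A reader might set 7 or 8 withdrawals against 16 events. The proper comparison is about 1 expected event.
- That withdrawals cluster in high-risk disease is plausible, but the documents do not say so.

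What does not stand is that the methods are harmless as named. The stated reason for the per-protocol analysis is unsound however the set is defined. The repeat assays at TE diagnosis exist only for children with TE, so they cannot classify exposure in both groups. Kaplan-Meier is planned as a description, without a comparison of defect groups in Table 3.

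**Conclusion.** The point holds in a limited form. Two methods named in the plan do not suit its design. A per-protocol set defined by therapy given as planned can drop TE cases, lowering incidence, risk difference and precision: from 25.0 to 21.6 points if 20% of cases are dropped, and to 15.3 if 50% are. Those shares are assumptions, and only a supplementary analysis is affected. LOCF has no sound use for defects classified at baseline or for a single event. If it were applied to TE status its effect would be small, at most about 1.3 of 25 points, given about 5% withdrawal that is equal between groups.

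The illustration uses the planning figures. The section on study progress reports 15% cumulative TE and a reduced sample of 131, but gives no figure for the high defect prevalence, so it cannot be rerun on those. The primary Fisher comparison is not shown to be materially wrong. The change is still worth making because it corrects stated methods at little cost.

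**What to change.** 1. Drop the per-protocol analysis for the defect comparison. If it is kept for the randomised asparaginase-type comparison, say so, and censor only at deviations that come before TE.
2. Delete LOCF. Use multiple imputation for missing baseline assays only.
3. Extend the planned Kaplan-Meier analysis to compare defect groups on time to first TE, censoring at withdrawal. Add a cumulative-incidence analysis with death, relapse and transplant as competing events (Gray's test or a cause-specific Cox model), and state how failure to achieve remission is classed. Report these alongside the Fisher test.

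The cost is wording and a little more analysis. The Clinical follow up and Secondary outcomes sections already provide for recording therapy changes, remission failure, relapse, transplant, withdrawal and death, so no new data items should be needed.

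### Kaplan-Meier for thrombosis-free survival does not estimate the cumulative incidence of TE when relapse, transplantation, induction failure and death end observation; the effect is small and limited to a descriptive estimate

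*Protocol article*

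**What the plan says.** The only time-to-event method named in the protocol article is in Methods for analysis: "Thrombosis-free survival will be estimated using Kaplan-Meier method". Other sections fix what that curve can see:

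- **Outcome** (Primary outcome): "Diagnosis of symptomatic TE in any location while on active ALL-therapy".
- **Follow-up** (Study duration): "till the completion of ALL-therapy on DFCI 05–01 study which is two years and one month", that is, 25 months.
- **Early end of observation** (Study withdrawal criteria): "Patients were withdrawn from thrombophilia study if they failed to achieve remission, develop recurrence of ALL while on ALL-therapy", and also "if they needed stem cell transplantation or were withdrawn from DFCI 05–01 study for any reason".
- **Relapse and death** (Secondary outcomes): the list includes "recurrence of disease or death due to any cause while on DFCI 05–01 ALL-therapy".
- **Target quantity** (Sample size, footnote to Table 4): "Difference in the cumulative incidence of TE in patients with and without prothrombotic defects".

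Table 3 assigns the primary aim to Fisher's exact test on binary TE, the first two secondary aims to regression, and the prevalence aim to percentages with confidence intervals. It does not mention Kaplan-Meier.

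**The concern.** A child who dies, relapses, goes to transplantation or fails induction can no longer have the outcome as defined. Censoring such a child assumes that their later risk of TE on protocol therapy matches that of the children who remain, but for them that risk no longer exists. One minus Kaplan-Meier then describes a hypothetical setting in which nobody leaves therapy for these reasons, and it lies above the proportion who actually develop TE.

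The word survival also allows a second reading, in which death is an event. The curve is then a valid estimate of freedom from TE or death, but it is not a TE incidence.

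The study works in absolute risk: the Sample size section ties its minimal important difference to a number needed to treat. A published curve that readers take for TE incidence should therefore be one.

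**Working it through.** **1. The plan's own figure.** The article gives no number for the Kaplan-Meier curve. Its power statement (more than 80% with 30 and 120 patients for a 25-point difference) can be checked without the curve:

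- Overall TE of 11% with 20% prevalence gives 31% against 6%, since 0.2 × 31 + 0.8 × 6 = 11. Fisher power is 92.2%.
- If 11% is instead the rate without a defect (36% against 11%), Fisher power is 84.5%.

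The statement holds on both readings, and the calculation compares proportions only.

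**2. Inputs for the bias.**

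- True cumulative incidence of TE, F = 15%. This is the preliminary figure in Study progress and modification to study protocol.
- Share with a competing event, c. This is an **assumption**, because the article does not give it. The low value of 5% is the withdrawal rate in Feasibility, which is not split by reason. The high value of 20% is the upper end of the all-cause mortality in Background, which has no time frame.
- Timing. The Abstract places about 90% of events in Consolidation. Placing 90% of TE before month 9 of 25 is an **assumption**. So is the spread of competing events: even hazard, or 70% before month 9.

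**3. Formulas.** With cause-specific hazards λ_TE(t) and λ_c(t), and S(t) the probability of being free of both:

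- true incidence: F = ∫ S(t) λ_TE(t) dt, and likewise for c
- what Kaplan-Meier reports if competing events are censored: 1 − exp(−∫ λ_TE(t) dt)

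The hazards are solved to reproduce F and c, then put into the second line. Two examples, with TE possible from month 0:

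- c = 5%, even: λ_TE = 0.016292 per month for 9 months, then 0.001140 for 16. The sum is 0.1649, so 1 − exp(−0.1649) = 15.2%.
- c = 20%, mostly early: λ_TE = 0.017541, then 0.001365. The sum is 0.1797, so 1 − exp(−0.1797) = 16.4%.

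**4. Results for a true 15%.**

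| Timing | c = 5% | c = 20% |
|---|---|---|
| TE from month 0, competing events even | 15.20% | 15.90% |
| TE from month 0, 70% of competing events before month 9 | 15.33% | 16.45% |
| TE from month 1, competing events even | 15.21% | 15.95% |
| TE from month 1, 70% of competing events before month 9 | 15.35% | 16.55% |

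Two cruder patterns have closed forms:

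- Constant hazards throughout, 1 − (1 − F − c)^(F/(F + c)): 15.4% and 16.9%.
- Every competing event before any TE, F/(1 − c): 0.15/0.95 = 15.8% and 0.15/0.80 = 18.8%. This is a ceiling and not a realistic case.

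**5. Higher TE risk.** In the four patterns of the table, a true 31% becomes 31.5–31.8% at c = 5% and 33.2–34.5% at c = 20%. A true 6% becomes about 6.1% and 6.3–6.6%. The excess in points grows with TE risk.

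**6. Death as an event.** The pilot counts under preliminary results of DFCI studies are 11 children with TE and 84 without, 5 of whom died. TE alone is 11/95 = 11.6%. TE or death is (11 + 5)/95 = 16.8%, which is 5.3 points more. The article gives no time frame for those deaths.

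**The case against.** The case against giving this weight is strong on several points.

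- **The curve serves no stated aim.** Table 3 gives every aim to another method. A reader might infer that Kaplan-Meier curves by defect, age and risk group will select children for a prophylaxis trial, but no section plans such curves. The high-risk group is to come from the difference in proportions and from the predictive model. This objection stands.
- **The needed quantity is available elsewhere.** The crude proportion in the Fisher table equals the cumulative incidence if withdrawn children stay in the denominator and nobody is otherwise lost. So it would be wrong to say that the plan has no route to TE incidence. This also stands.
- **The censoring rule is not stated**, and an article may leave it to the full protocol. That is why both readings are worked above. The silence itself is not the point; the named estimator is, because neither reading of it yields TE incidence.
- **The size is modest.** At 15% and n = 150 the 95% half-width is 1.96 × √(0.15 × 0.85/150) = 5.7 points, against an excess of 0.2–1.6 points. A reader might instead take the 44% TE in older children and reach up to 49.3%. That needs 20% mostly early competing events on top of a rate from a pilot of 91. The same section also gives 12% for that age group from 906 children, with the caveat that TE was not consistently collected.
- **More competing events in high-risk or older children** is plausible, but the article gives no figure for it.

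What remains is that an unsuitable estimator is named where a suitable one costs almost nothing.

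**Conclusion.** The point holds as a low-cost improvement to a supporting descriptive estimate. By the article's own definitions, induction failure, relapse, transplantation and death compete with TE on active therapy.

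- **If they are censored**, a true 15% would be shown as about 15.2–15.4% with 5% competing events and 15.9–16.6% with 20%. These figures rest on the assumed share and timing of competing events.
- **If death is an event**, the distortion is larger: about 5 points on the pilot counts, assuming that those deaths fell within the therapy window.

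The Fisher test, the logistic models and the power statement are unaffected. A reader might also infer that the preliminary 15%, which contributed to the reduction to 131 patients, is inflated for this reason. The article does not say whether that figure is a Kaplan-Meier estimate or a crude proportion, so the inference is not supported.

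**What to change.** Replace the Kaplan-Meier sentence with one that says:

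- the cumulative incidence of first symptomatic TE will be estimated by the Aalen-Johansen method;
- death, induction failure, relapse and transplantation are competing events;
- children are censored at the end of therapy, at loss of contact, or at withdrawal from DFCI 05–01 for other reasons.

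If TE-free survival is also wanted, report it separately by Kaplan-Meier and state that death is an event.

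The cost is wording only. Clinical follow up already monitors induction failure, recurrence, transplantation and continued enrolment, and death is among the Secondary outcomes; confirm that the case report forms hold the dates. Software beyond SPSS 14 may be needed.
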